
|                      |                                                                                                                                                                                                                                                                                                                                                                                                                                                                                                                                                                                                                                                                                                                                                                                                                                  |
|----------------------|----------------------------------------------------------------------------------------------------------------------------------------------------------------------------------------------------------------------------------------------------------------------------------------------------------------------------------------------------------------------------------------------------------------------------------------------------------------------------------------------------------------------------------------------------------------------------------------------------------------------------------------------------------------------------------------------------------------------------------------------------------------------------------------------------------------------------------|
| Objective(s): | 
This study compares under controlled conditions if different flow rates affect apnoea time after induction of anaesthesia and how CO2 clearance is influenced. Furthermore, this study enables to quantify the effects of increased pCO2 on cerebral perfusion.
 
Our primary hypothesis states that any of the three intervention is non-inferior to HFNCT regarding clearance of CO2 (ventilatory effect).
                                                                                                                                                                                                                                                                                                                                                                        |

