| Outcome(s):   | 
Primary outcome: mean ptcCO2 increase in mmHg/min during apnoea time, measured transcutaneously.
 
Secondary outcomes: in case of desaturation within the predefined apnoea time: time (in seconds) until desaturation from SpO2 100% to 92%, measured by pulse oximetry. Changes in ptcO2, paO2 and paCO2 in mmHg/min, blood gas analysis parameters, upper airway patency, influence of jaw thrust vs. continuous laryngoscopy on CO2 clearance during HFNCT, changes in brain oxygenation (measured by near infrared spectroscopy (NIRS)) during apnoea time, changes in electrical impedance tomography (EIT) to validate ventilatory effect and pulse contour analysis to monitor cardiac output.
 |
| Study design: | 
Prospective, single centre, randomised controlled trial with four groups:
 

1) high flow 70 l/min of oxygen, using jaw thrust

2) high flow 70 l/min using continuous laryngoscopy

3) medium flow 10 l/min using jaw thrust

4) low flow 2 l/min using jaw thrust

                                                                                                                                                                                                                                                                                                                                                                                                                                                                                     |

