THRIVE has shown to be a suitable method to prolong apnoea with stable O2 saturation [2, 3]. Despite promising pilot results with high-flow nasal cannula therapy, it is unknown whether this technique is superior to low-flow nasal cannula therapy. Especially the claimed ventilatory effect has not yet been provided with sufficient data. It is thought to happen through turbulences caused by the high flow, that continue down through the trachea into the alveoli. This turbulence is said to wash out CO2 because slower increase of CO2 has been described using THRIVE vs. normal apnoea. However, this data of normal apnoea was already acquired in 1959 by Frumin et al. on only 8 healthy patients [4]. Since then, many things, including technology and patient factors have changed and this data therefore has only limited application today.

Especially the CO2 clearance under different flow rates has yet to be thoroughly examined. This is important, as increased CO2 can cause a multitude of effects like acidosis and altered cerebral blood flow [4, 11, 14]. Our study will also examine the effect of increasing paCO2 on cerebral perfusion using NIRS.

Furthermore, we will compare HFNCT at 70 l/min performing jaw thrust, with a group of patients, who's mouths will be opened using continuous video laryngoscopy, which is a standard procedure today for laryngeal surgery. In our study, we will only apply the minimal strength required in order to keep the airway patent, which can be visually confirmed using the video-monitor. Whether laryngoscopy compared to jaw thrust makes any difference in oxygenation or CO2 increase has yet to be examined.

This study investigates under controlled circumstances the concept of THRIVE to prolong apnoea time without desaturation. With our findings, we hope to improve airway management safety. Furthermore, this study enables us to better understand physiology behind apnoeic oxygenation and the influence of different nasal flow rates. Our study's extensive setup also allows us to measure the effects of increased CO2 on cerebral blood flow and cardiac output.

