### **4.3 Secondary Objectives**

Secondary study objective is to evaluate the mean duration of apnoea. Also, changes in EIT, NIRS, BP and heart rate are measured. We will also assess airway patency while performing jaw thrust. This can be either patent or not-patent.

We also want to monitor the effect of increased  $CO_2$  on the cardiac output via the simultaneously obtained pulse contour analysis using either FlowTrac by Edwards Lifescience, Irvine, California, or LiDCO by LiDCO Ltd, London, UK.

Bilateral frontal cerebral NIRS measurements will be performed to determine the effect of high  $CO_2$  on brain perfusion. A NIRO monitor by Hamamatsu, Japan, will be used, which delivers brain oxygenation as a surrogate of brain perfusion, as well as the percentage of oxygenated and deoxygenated blood in the sampled tissue.

To ensure absence of respiratory movements, complete neuromuscular blockage will be confirmed using train-of-four (TOF) which should be 0 throughout the experiment. Additional muscle relaxants may be administered if necessary. Respiration must be avoided at all times, since otherwise our results would be unusable.

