## 10. STATISTICAL METHODS

### 10.1 Hypothesis

Null hypothesis: The difference of the mean increase of  $p_{tc}CO_2$  between any of the three intervention groups and the control group is at least 0.3 mmHg/min, the control group being lower.

Primary hypothesis: the difference of the mean increase of  $p_{tc}CO_2$  between the groups is less than 0.3 mmHg/min (non-inferior margin), one-sided testing. This hypothesis was based on a small clinical pilot study that showed no differences regardless of flowrate or mouth opening (jaw-thrust vs. laryngoscopy).

Secondary outcome hypothesis: The number of patients not tolerating the apnoea time of 15 minutes is not significantly higher in any of the three intervention groups.

Secondary outcome hypothesis: no significant changes in vital parameters such as cerebral perfusion will be recorded.

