### 10.2 Determination of Sample Size

We assumed that with maximal flow of 70L O2/min and maximal mouth opening, there would be the least increase of  $p_{tc}CO_2$ /min. Patel et al. showed an increase of only 1.13mmHg using this technique [2]. However, this was  $etCO_2$  instead of  $p_{tc}CO_2$ . According to Gustafson et al., who measured  $p_{tc}CO_2$  as well as  $p_aCO_2$ , the  $CO_2$  increase was in fact 1.8mmHg/min, with a standard deviation of 0.35mmHg [3]. This correlated very well with our own findings in our pilot study (not published).

Using a non-inferiority design, a difference of means of 0.3mmHg/min, a standard deviation of 0.35mmHg/min, an alpha of 0.025 (one-sided) and a power of 80%, the necessary sample

size calculates to 22 patients per group. Therefore, we will include 25 patients in each group to account for possible drop outs. A value of 0.3mmHg/min would still only result in a difference in increase of 9mmHg in 30 minutes of apnoea time. We defined this as measurable, but still clinically acceptable, because the normal range of standard arterial pCO2 is 11mmHg (35-46 mmHg) [6].

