### **10.3 Planned Analyses**

#### **10.3.1 Datasets to be analysed, analysis populations**

Distribution of data will be checked using qq-plots and swilk command in stata, normal distributed data will be presented as means and standard deviation, otherwise median and interquartile range will be used. Proportions will be presented as numbers and percentage. Analytical statistics uses Mann-Whitney u-tests and Students t-test, according distribution, or ANOVA and Kruskal-Wallis for multiple groups. Each of the groups will a-priori be compared to the control group independently, without correction of multiple comparisons. Other multiple comparisons or subgroup-analyses will be performed using correction factors. Proportions will be compared by Chi-square tests or Fisher's exact test. As sensitivity analyses, we will do regression analyses, using mixed effects linear regressions.

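### The main tests named in 10.3.1 compare arms expected to have nearly equal CO2, so they cannot quantify the effect of raised CO2 on cerebral perfusion and cardiac output; the matching hypothesis in 10.1 names no comparator

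*Protocol*

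**What the plan says.** **Objective.** The synopsis (Objective(s)) states that "this study enables to quantify the effects of increased pCO 2 on cerebral perfusion". Section 3.1 says "Our study's extensive setup also allows us to measure the effects of increased CO 2 on cerebral blood flow and cardiac output". Section 4.3 says that bilateral frontal "NIRS measurements will be performed to determine the effect of high" CO2 on brain perfusion, and it also lists the effect of increased CO2 on cardiac output by pulse contour analysis.

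**Outcome.** The synopsis (Outcome(s)) lists "changes in brain oxygenation (measured by near infrared spectroscopy (NIRS)) during apnoea time".

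**Hypothesis.** Section 10.1 states that "no significant changes in vital parameters such as cerebral perfusion will be recorded". It gives neither groups nor time points, and it names cerebral perfusion but not cardiac output.

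**Analysis.** Section 10.3.1 lists Mann-Whitney and t-tests, ANOVA and Kruskal-Wallis, and adds: "Each of the groups will a-priori be compared to the control group independently". Mixed-effects linear regression appears only as a sensitivity analysis, with no outcome or covariate named.

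**Expected CO2 by arm.** Section 10.1 bases the primary hypothesis on a "small clinical pilot study that showed no differences regardless of flowrate or mouth opening (jaw-thrust vs. laryngoscopy").

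**The concern.** For this objective CO2 is the exposure, and perfusion and cardiac output are the responses. What is randomised is flow rate and airway manoeuvre, and the protocol expects neither to change the CO2 rise by much. Arm is then a poor stand-in for CO2. The closer the arms are in CO2 rise, as the trial expects, the less any arm-versus-control test can show about CO2.

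The hypothesis adds to the difficulty. It predicts an absence of significant change, with no margin and no stated comparison, so a non-significant result from an insensitive contrast could be taken as confirming it. This bears on safety: section 2.1.2 relies on NIRS for assurance that cerebral perfusion stays normal during hypercapnia, and section 4.4 lists NIRS under the safety objectives.

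**Working it through.** **Inputs from the protocol**
- Section 10.2: CO2 rise of 1.8 mmHg/min. The sample size uses "a difference of means of 0.3mmHg/min, a standard deviation of 0.35mmHg/min, an alpha of 0.025 (one-sided) and a power of 80" per cent, giving 22 per group.
- Section 8.5.2: apnoea ends at 15 minutes at the latest.
- Section 6.1: 25 patients per group, 100 in all; NIRS and cardiac output recorded continuously.
- Section 8.5.3.2: blood gases awake, at the start of apnoea, at 1 minute, then every 2 minutes (ten in total).

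**Assumptions (the protocol gives no figure)**
- The full CO2 rise changes the response by d standard deviations of the change, with d from 0.5 to 3.
- The response is proportional to CO2, with the same SD in both kinds of test.
- Tests are at two-sided 0.05. The protocol's alpha applies to the primary outcome only.

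**Step 1: the protocol's own figure.** n = 2 × (1.960 + 0.842)² × 0.35² / 0.3² = 21.4, rounded up to 22 per group. The stated size reproduces. No calculation is given for perfusion or cardiac output.

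**Step 2: the CO2 contrast each comparison offers**
- Within a patient over 15 minutes: 1.8 × 15 = 27 mmHg.
- Between arms, as expected from the pilot: about 0.
- Excess of an arm over control at the margin: 0.3 × 15 = 4.5 mmHg.
- Ratio: 4.5 / 27 = 1/6. It does not depend on the duration if the arms stop at the same time.

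**Step 3: power of an arm-versus-control t-test, 25 against 25.** At the margin the standardised difference is d/6, with non-centrality (d/6) × √(25/2). If the arms have equal CO2, the test rejects 5% of the time whatever CO2 does.

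| d over 27 mmHg | d/6 | Power, arm v control at the margin |
|---|---|---|
| 0.5 | 0.083 | 6.0% |
| 0.8 | 0.133 | 7.5% |
| 1 | 0.167 | 8.9% |
| 1.5 | 0.25 | 13.9% |
| 2 | 0.333 | 21.1% |
| 3 | 0.5 | 41.0% |

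For 80% power at d = 1, n = 2 × (1.960 + 0.842)² / (1/6)², or 566 per arm. A four-arm ANOVA with one arm at the margin does no better: 8% at d = 1, 19% at d = 2 and 40% at d = 3.

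**Step 4: a within-patient test of change.** With non-centrality d × √n, a single arm of 25 has 67% power at d = 0.5, 97% at 0.8 and 99.8% at 1. All 100 patients give 99.9% at d = 0.5. This is power to detect change over apnoea from any cause, not power to isolate CO2.

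**Step 5: how far CO2 can be separated from time.** Take slopes with mean 1.8 and SD 0.35 at 1, 3, …, 15 minutes. The times have mean 8, variance 21 and mean square 85.
- Covariance of CO2 with time: 1.8 × 21 = 37.8.
- Variance of CO2: (1.8² + 0.35²) × 85 − (1.8 × 8)² = 78.45.
- Correlation: 37.8 / √(21 × 78.45) = 0.93.

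This leaves out baseline spread and measurement error, which would lower it.

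**The case against.** The strongest reply is that the protocol nowhere says this hypothesis is tested between arms. The hypothesis just before it in 10.1 refers to the intervention groups; this one does not. The synopsis outcome reads naturally as change within a patient. On that reading a large CO2 effect would very probably be significant. Section 10.3.1 is a general list that assigns no test to NIRS or cardiac output. It does name mixed-effects regression, and the details may stand in an analysis plan that is not shown.

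Much of this stands. A reader might infer that the protocol commits itself to an arm comparison for this objective. The text does not support that; the inference comes only from the list of tests. The lack of a stated reference time point is likewise not a fault in itself.

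A reader might also infer that success on the primary hypothesis holds all arms within 0.3 mmHg/min of each other. It does not. The margin is one-sided and against control: it limits only how much faster than control an arm may rise. It does not limit how much slower an arm may rise, nor the gap between two intervention arms. Near-equality of the arms rests on the pilot statement alone.

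The power figures do depend on an assumed effect size, and stops before 15 minutes would shorten the 27 mmHg exposure.

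What the reply does not remove is the mismatch. If the hypothesis is within patient, 10.3.1 names no main test explicitly suited to it and ranks the one fitting model as sensitivity only. If it is between arms, the contrast carries almost no CO2 information. On either reading, non-significance is offered as the finding.

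**Conclusion.** The point holds as a mismatch between objective, hypothesis and named tests. The objective concerns CO2, the hypothesis names no comparator, and the main tests compare groups expected to have nearly equal CO2. The CO2 contrasts of about 27 mmHg within a patient, and from about zero as expected to a 4.5 mmHg excess over control at the margin, follow from the protocol's own figures over a full 15 minutes. The power of about 9% to 21% rests on assumed effects of 1 to 2 SD, a response proportional to CO2 and two-sided 0.05. At an assumed 3 SD it is still only 41%.

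It would go too far to say that the trial will report no effect of hypercapnia. Power is low rather than zero, and a within-patient analysis remains open. The supported conclusion is that a non-significant arm comparison would be almost uninformative about CO2. This concerns a secondary objective; the primary comparison is unaffected. It should be changed, because the data for a better analysis are already being collected.

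**What to change.** - In 10.3.1, make a within-patient mixed-effects model, pooled over the four arms, the main analysis for this objective. Regress NIRS and cardiac output on the paired paCO2 from the serial blood gases, with the start of apnoea as reference and arm as a covariate.
- In 10.1, replace the prediction of no significant change with an estimate and 95% confidence interval per 10 mmHg paCO2, and name cardiac output as well as cerebral perfusion.
- Keep arm comparisons of these outcomes as secondary.
- Do not adjust blood pressure for mean arterial pressure, which would be circular. For NIRS and cardiac output, show models with and without mean arterial pressure: section 2.1.2 says that CO2 has haemodynamic influence, so pressure may mediate the response.
- Report the result as an association. CO2 rises almost in step with elapsed time and no arm stays normocapnic, so the estimate cannot be fully separated from time, drug and oxygenation effects.

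The cost is protocol wording and some modelling. No extra patients, measurements or changes to care are needed.

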### 10.2 Determination of Sample Size

We assumed that with maximal flow of 70L O2/min and maximal mouth opening, there would be the least increase of  $p_{tc}CO_2$ /min. Patel et al. showed an increase of only 1.13mmHg using this technique [2]. However, this was  $etCO_2$  instead of  $p_{tc}CO_2$ . According to Gustafson et al., who measured  $p_{tc}CO_2$  as well as  $p_aCO_2$ , the  $CO_2$  increase was in fact 1.8mmHg/min, with a standard deviation of 0.35mmHg [3]. This correlated very well with our own findings in our pilot study (not published).

Using a non-inferiority design, a difference of means of 0.3mmHg/min, a standard deviation of 0.35mmHg/min, an alpha of 0.025 (one-sided) and a power of 80%, the necessary sample

size calculates to 22 patients per group. Therefore, we will include 25 patients in each group to account for possible drop outs. A value of 0.3mmHg/min would still only result in a difference in increase of 9mmHg in 30 minutes of apnoea time. We defined this as measurable, but still clinically acceptable, because the normal range of standard arterial pCO2 is 11mmHg (35-46 mmHg) [6].

### **10.3 Planned Analyses**

#### **10.3.1 Datasets to be analysed, analysis populations**

Distribution of data will be checked using qq-plots and swilk command in stata, normal distributed data will be presented as means and standard deviation, otherwise median and interquartile range will be used. Proportions will be presented as numbers and percentage. Analytical statistics uses Mann-Whitney u-tests and Students t-test, according distribution, or ANOVA and Kruskal-Wallis for multiple groups. Each of the groups will a-priori be compared to the control group independently, without correction of multiple comparisons. Other multiple comparisons or subgroup-analyses will be performed using correction factors. Proportions will be compared by Chi-square tests or Fisher's exact test. As sensitivity analyses, we will do regression analyses, using mixed effects linear regressions.

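### The analysis section does not tie the primary comparison to the 0.3 mmHg/min margin, and its normality-driven switch to Mann-Whitney would change the quantity tested

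*Protocol*

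**What the plan says.** Section 10.1 of the protocol states a margin null on means. For an intervention arm against control, the difference in mean ptcCO2 increase "is at least 0.3 mmHg/min, the control group being lower". The alternative is that the difference "is less than 0.3 mmHg/min (non-inferior margin), one-sided testing".

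Section 10.2 sizes the trial for this test, using "a difference of means of 0.3mmHg/min, a standard deviation of 0.35mmHg/min", and "an alpha of 0.025 (one-sided) and a power of 80" per cent. The result "size calculates to 22 patients per group", raised to 25 for drop-outs.

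Section 10.3.1 describes the analysis, and the synopsis (Statistical Considerations) repeats it. Distribution is checked by Q-Q plots and the Shapiro-Wilk command in Stata. Then: "Analytical statistics uses Mann-Whitney u-tests and Students t-test, according distribution, or ANOVA and Kruskal-Wallis for multiple groups". Each intervention group is compared with control separately and without multiplicity correction. Mixed effects linear regressions are the sensitivity analyses. The section mentions no margin, one-sided level, confidence interval or decision rule, and it does not separate the primary outcome from the others.

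**The concern.** The hypothesis and the sample size concern a difference in means, measured against 0.3 mmHg/min. The test rule in section 10.3.1 does not carry that question through, in two respects.

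- **The margin is not applied.** In their default form all four named tests address equality, and the section does not say that the primary test is run against 0.3. A non-significant result could then be reported as non-inferiority. Conversely, a small significant difference inside the margin could be reported as failure.
- **The quantity can change after the data are seen.** If the distribution check fails, the comparison moves to Mann-Whitney. That test does not estimate a mean difference, and the protocol gives no margin on a rank or location-shift scale. ANOVA and Kruskal-Wallis test equality across groups and cannot show non-inferiority.

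The trial's primary conclusion rests on this comparison, and a later analysis plan that followed section 10.3.1 would inherit the conflict.

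**Working it through.** **Inputs.** From sections 10.1 and 10.2: margin 0.3 mmHg/min, SD 0.35 mmHg/min, one-sided alpha 0.025, power 80%, 22 per group needed and 25 enrolled. A true difference of 0 is not stated as an input. It is inferred from the "small clinical pilot study that showed no differences regardless of flowrate or mouth opening" (section 10.1).

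**1. The plan's own figure.**
n = 2(z₀.₉₇₅ + z₀.₈₀)² SD² / margin² = 2 × (1.960 + 0.842)² × 0.35² / 0.3² = 21.4, rounded up to 22. This reproduces. A two-sided 5% test to detect a difference of 0.3 also gives 22, so the number alone does not show which test was meant. The wording of 10.1 and 10.2 does.

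**2. The t-test against the margin.** Reject the null if (d − 0.3)/SE is below −t₀.₉₇₅ with 2n − 2 df, where d is the observed difference (intervention minus control) and SE = 0.35√(2/n). From the noncentral t distribution, power at a true difference of 0 is 79.3% (n = 22) and 84.4% (n = 25). Type I error at a true difference of 0.3 is 2.5% per comparison. This branch does what the design promises.

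**3. The same test against zero, with non-significance read as non-inferior.** This reading is conditional; the protocol does not state it. At a true difference of 0.3:

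| n per arm | SE | noncentrality 0.3/SE | P(two-sided p > 0.05) |
|---|---|---|---|
| 22 | 0.1055 | 2.84 | 20.7% |
| 25 | 0.0990 | 3.03 | 15.6% |

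The planned error is 2.5%. In the other direction, at a true difference of 0.15, which is inside the margin, the zero-difference test is significant in 31.8% of trials at n = 25.

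**4. Where the two readings part.** At n = 25 the expected 95% CI half-width is 2.011 × 0.0990 = 0.199. Non-inferiority needs d below 0.3 − 0.199 = 0.101, while the zero-difference test is non-significant for any d up to 0.199. Observed differences from about 0.10 to 0.20 therefore lead to opposite conclusions.

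**5. How often the switch would operate.** The protocol gives no threshold for the distribution check. Assuming Shapiro-Wilk at 5% in each of two arms, exactly normal data trigger it in 1 − 0.95² = 9.75% of comparisons. With one arm lognormal (sigma 0.6) and n = 25, it is triggered in about 77%.

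**6. What the switch does even if the margin is applied.** This is a simulation at n = 25, SD 0.35 in both arms and a true mean difference of 0.3. The Shapiro-Wilk rule (5% per arm) selects a t-test or a Mann-Whitney test, each shifted by 0.3, at one-sided 0.025. The skewed shape is an assumed lognormal with sigma 0.6; the protocol gives no information on shape.

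| Shapes | Error at the margin |
|---|---|
| Both arms normal | about 2.5% |
| Both arms equally skewed | about 2.6% |
| Only the intervention arm skewed | about 6.3% |
| Only the control arm skewed | about 0.9% |

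In the third row the shifted t-test alone gives 3.6% to 3.9%, depending on the run. The error moves with the difference in shape, because Mann-Whitney then no longer tests the difference in means.

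**The case against.** Section 10 can be read as a whole. Section 10.1 supplies the null, the margin and the one-sided direction, and 10.2 supplies the level, so 10.3.1 need not repeat them. A Student t-test against 0.3 is the test that the sample size was built on. The sentence listing the tests is generic and covers all outcomes. The mixed effects regression can give a mean difference whichever test is chosen. The form of the interval and the decision rule commonly sit in a statistical analysis plan, which is not shown.

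Much of this stands. A reader might infer that the protocol plans tests of zero difference and so cannot reach its stated conclusion. The text does not support that: 10.3.1 states no null value, 10.1 states the right one, and the t-test branch can be run correctly. A reader might also infer that ANOVA or Kruskal-Wallis is the primary test. They are offered for several groups at once, and nothing assigns them the primary claim. The wording in 10.1 that treats non-significance as the conclusion belongs to secondary hypotheses. It shows that the misreading is possible, not that it is planned for the primary outcome.

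It is also fair that a shifted Mann-Whitney test can be compared with 0.3 if both arms share a shape, and that the 6% figure is one selected case.

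What the objection does not remove is the switch itself. It is a stated rule, not an omission left to a later document. When it operates, it replaces the mean difference of 10.1 and 10.2 with a comparison for which no margin is given. The regression is only a sensitivity analysis and has no margin attached either.

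**Conclusion.** The point holds in this form: section 10.3.1 and the synopsis do not link the primary comparison to the margin and one-sided 0.025 level of 10.1 and 10.2, and the distribution-driven switch to Mann-Whitney would change the quantity tested. ANOVA and Kruskal-Wallis should not carry the primary claim.

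The size depends on how the paragraph is applied:

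- If the t-test is used against 0.3, there is no loss.
- If the tests are used against zero and non-significance is read as non-inferior, an arm worse by the full margin passes in about 16% of trials at 25 per arm (21% at 22) instead of 2.5%. This assumes SD 0.35 and normal data.
- If the rule is applied with the margin, error stays near 2.5% under a common shape and runs from about 1% to 6% if one arm alone is skewed. This rests on an assumed lognormal shape with sigma 0.6 and a 5% Shapiro-Wilk threshold.

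The second and third figures show the cost of particular readings or data shapes. They are not the operating characteristics of the plan as a whole.

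**What to change.** In section 10.3.1 and in the synopsis, state the primary analysis separately from the generic list of tests. Suggested wording:

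*For each of the three comparisons with control, the primary analysis is the difference in mean ptcCO2 slope (intervention minus control) with a two-sided 95% confidence interval. Non-inferiority is concluded if the upper limit is below 0.3 mmHg/min. This analysis is used regardless of the normality check. Rank-based tests are used only for sensitivity analyses or secondary outcomes.*

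Keep ANOVA and Kruskal-Wallis out of the primary claim. The choice of model, or of a bootstrap interval if residuals are skewed, can be left to the analysis plan.

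The cost is one paragraph in two places, settled before the data are seen. The sample size stays at 22 per group with 25 enrolled, and no procedure changes.
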